### Quality control

The trial protocol has been reviewed and revised by experts in acupuncture, neurology, and statistics. Standard operating procedures (SOPs) will be developed in advance, and training sessions will be conducted prior to the study commencement to provide standardized training for researchers at each center. This ensures that all researchers are familiar with the study process and specific implementation details. Trial participants should remain consistent, and both recording methods and evaluation criteria must be standardized to ensure uniformity in scale assessments, data management, and CRF completion. Data monitors will conduct quality control checks every 3 months at each research center to ensure strict adherence to all elements of the study protocol and the accuracy of complete information. Quality control analysis reports will be generated following each inspection.

## Discussion

Recurrent vertigo episodes in PCIS patients increase recurrence and mortality rates, creating a cycle of worsening health. This not only heightens the health burden on individuals but also imposes significant economic pressures on healthcare systems and society.

The DHI is widely acknowledged as the gold standard for assessing patients with vertigo symptoms, with well-documented validity, reliability, and reproducibility in clinical trial settings. This comprehensive questionnaire evaluates the precipitating physical factors associated with vertigo and assesses the functional and emotional impacts of vestibular impairment. The primary aim of the DHI is to quantify the disability and impairment caused by vertigo, providing insights into its effects on patients’ daily activities (27). The DHI consists of three main components: physical symptoms of dizziness and vertigo, vestibular dysfunction, and emotional impact, and serves as a valuable tool in both clinical practice and research for evaluating the multidimensional impact of vertigo on patients’ quality of life. Accordingly, the DHI was selected as the primary outcome in this trial because it represents the most patient-centered and clinically relevant measure for capturing the overall burden of dizziness in patients with posterior circulation ischemic stroke. This choice is consistent with international consensus and core outcome recommendations for clinical trials involving vertigo.

Pearson’s analysis showed that the DHI and DARS had a good correlation and were consistent in the assessment of vertigo patients, and all of them could be used to assess the degree of vestibular function impairment (28). The DARS scale is comprehensive, highly reliable, easy to understand. In addition, dizziness diaries are helpful for analyzing patients’ subjective symptoms: they enable us to confirm whether the characteristics of the attacks meet the diagnostic criteria, and they also facilitate more effective monitoring of treatment outcomes, which is especially important due to the non-specific episodic nature of the disorder. Furthermore, the use of dizziness diaries has enabled a prospective observational approach in this study (29). Nevertheless, subjective patient-reported outcomes are inevitably affected by individual symptom perception, emotional state, and psychological factors. In acupuncture trials, these subjective responses are particularly prone to the influence of treatment expectation and non-specific contextual effects, which may partially contribute to perceived improvement. Although we quantitatively assessed treatment expectation to explore its potential influence, such assessment alone cannot completely exclude confounding from expectancy or placebo-like effects. Thus, caution should be exercised when interpreting the observed treatment effects, with due consideration given to the inherent limitations of subjective outcome measures.

To reduce reliance on subjective patient-reported outcomes, this trial places strong emphasis on objective hemodynamic and imaging biomarkers, including TCD, sMRI, and ASL-MRI. However, research on the effects of acupuncture on cerebral blood flow and brain imaging remains relatively limited and requires further development and refinement (30). At present, the underlying cerebral mechanisms associated with acupuncture in the treatment of vertigo following posterior circulation ischemic stroke have not been fully elucidated, highlighting the need to advance related research. Therefore, this study not only evaluates the therapeutic efficacy of acupuncture for PCIS with vertigo, but also employs TCD, sMRI and ASL-MRI to provide a more in-depth assessment of the potential hemodynamic mechanisms and subtle structural changes associated with post-stroke vertigo. By doing so, this approach not only provides a scientific basis for acupuncture in treating PCIS with vertigo, but also explores its underlying therapeutic mechanisms, offering new insights into clinical management and potentially improving treatment outcomes.

Both pragmatic and explanatory randomized controlled trials play important roles in evaluating healthcare interventions. Explanatory trials are designed to establish the absolute efficacy of a treatment intervention (31). In acupuncture research, the primary goal of an explanatory trial is to determine whether acupuncture is superior to a placebo. A sham acupuncture control in clinical trials should meet three key criteria: (1) the sham intervention has little or no specific therapeutic effect; (2) the needles are applied at non-effective locations; and (3) participants are unable to distinguish between the sham and real acupuncture treatments. To rigorously satisfy these criteria and resolve the inconsistent efficacy outcomes reported in previous sham acupuncture-controlled trials, our sham acupuncture protocol was developed based on evidence-based principles for device selection and non-acupoint localization specifically tailored to acupuncture RCTs for brain function-related disorders (32). For such disorders (including PCIS with vertigo), the Streitberger non-penetrating placebo needle is the preferred sham device. Non-acupoint sites are also recommended to be located in non-meridian regions adjacent to genuine acupoints; this approach can strengthen the placebo effect in the control group and lower the risk of false-negative outcomes in clinical trials (33). Additionally, the specific localization of our non-acupoint sites (1–1.5 cun lateral to the actual acupoints along the meridians) was determined in accordance with standardized non-acupoint selection criteria validated in relevant reference literature (34). Considering these principles, we selected a non-meridian, non-acupoint location adjacent to the acupoints used in the acupuncture group for the sham intervention. To enhance blinding, we will use a blunt-tipped placebo needle that mimics the sensation of real acupuncture without penetrating the skin. Upon contact with the skin, the tip of the placebo needle creates a slight pricking sensation, but does not pierce the skin. Combined with the perceived insertion and retention, participants are likely to perceive this as genuine acupuncture, thereby improving the effectiveness of blinding. Although non-acupoints adjacent to meridians were adopted for sham administration, potential mild physiological effects from such locations cannot be fully excluded. This sham design represents the most feasible and widely validated approach for brain-related disorders, but residual non-specific effects may still exist and should be acknowledged when interpreting specific efficacy.

Given that betahistine is commonly used in the clinical management of vertigo following PCIS, we have also included a medication control group treated with this drug, allowing for a comparative evaluation of the efficacy of acupuncture versus standard pharmacological therapy. While betahistine is predominantly indicated for peripheral vestibular disorders, its inclusion as an active comparator in this trial is methodologically sound and clinically informative for central vascular vertigo. This choice does not imply an assumption of superior efficacy but rather reflects real-world clinical practice, where no guideline-directed pharmacotherapy exists for PCIS with vertigo. Using the most widely adopted clinical agent as a comparator enables a pragmatic effectiveness comparison rather than an explanatory efficacy trial, which is more generalizable to routine care. Furthermore, our three-group design with true acupuncture, sham acupuncture, and betahistine permits simultaneous dissection of specific needling effects, non-specific placebo responses, and the actual clinical performance of standard care. Even if betahistine shows only mild or placebo-like effects in this study population, our trial will still produce high-quality evidence to clarify the added value of acupuncture and support evidence-based clinical decisions for these patients.

Notably, the present three-arm trial was established with a hierarchical study objective design to clearly differentiate explanatory from comparative effectiveness purposes. The primary comparison between manual acupuncture and sham acupuncture was specifically designated to evaluate the specific efficacy of acupuncture, whereas comparisons between acupuncture and western medication were defined as secondary analyses. This clearly predefined hierarchical structure minimizes potential ambiguity in the interpretation of study outcomes and reinforces the scientific validity and rigor of the trial design.

Necessarily, this study also has several limitations. First, participants in the western medication group could not be blinded due to the nature of oral intervention, whereas those in acupuncture groups were blinded. This incomplete blinding may introduce expectation bias and affect the objectivity of subjective outcomes. Future trials are expected to use a double-dummy design to achieve full blinding across all groups. Second, this study focused primarily on changes in cerebral blood flow and brain structure, without exploring potential cerebral functional mechanisms in PCIS patients with vertigo. Third, subjective outcome assessments rely on participant self-report which may be affected by individual perception and recall bias due to the lack of objective vestibular function tests. Fourth, the follow-up duration is relatively short and fails to capture the long-term therapeutic efficacy and recurrence risk of vertigo symptoms in PCIS patients.

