### Randomization and blinding

A random number will be generated with the R software (V.4.3.3) and concealed in opaque random envelopes. The envelopes will be prepared by a third party in advance, with the sequence number labeled on the surface and the random number and group allocation information sealed in. The random envelopes will be preserved by special personnel who are not involved in treatment and evaluation. Participants are randomly assigned in a ratio of 1:1:1 to manual acupuncture (MA) group, sham acupuncture (SA) group, and western medication (WM) group.

Given the use of two distinct acupuncture techniques in this trial, the acupuncturist will be aware of the group allocation for each participant. However, identical auxiliary devices will be used in both the acupuncture and sham acupuncture groups to maintain blinding for participants. Participants in both groups will remain unaware of their specific group assignment. Furthermore, outcome assessors and statisticians will be blinded to group allocations throughout the study to minimize bias. To maintain blinding, all researchers will undergo identical training prior to the trial, and treatments will be administered in separate rooms for each participant. It should be noted that participants in the medication group will not be blinded.

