### Intervention and comparison

All patients will receive guideline-based interventions (22, 23) for the secondary prevention of ischemic stroke which include: 1) management of risk factors such as blood pressure and blood glucose; 2) targeted treatments: administration of aspirin for antiplatelet therapy or warfarin for anticoagulation, as appropriate, along with atorvastatin for lipid regulation and plaque stabilization; 3) patient education on dietary and lifestyle modifications. Specific interventions for each group are as follows: the MA group will receive manual acupuncture in addition to standard secondary prevention treatment; the SA group will receive sham acupuncture alongside standard secondary prevention treatment; and the WM group will receive betahistine (24) in conjunction with standard secondary prevention treatment.

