### Sample size calculation

As reported in previous studies (8), the mean DHI score for patients treated with betahistine mesilate was 30. For the purpose of sample size estimation, we adopted the clinically meaningful difference derived from our primary comparison: manual acupuncture versus sham acupuncture, assuming a mean DHI score of 21 in the manual acupuncture group, 33 in the sham acupuncture group, with a standard deviation of 20. A 12-point difference in DHI total score between manual acupuncture and sham acupuncture was regarded as clinically meaningful, since the minimal clinically important difference (MCID) for DHI total score has been established as 11 points (26). The trial will include three groups in a 1:1:1 ratio. Using a twotailed test with a category 1 error of 0.05 and a statistical efficacy of 90%, One-Way Analysis of Variance (ANOVA) F-Tests was employed by PASS software (Power Analysis and Sample Size, version 15). The calculations indicate that a minimum of 66 participants per group is required, totaling 198 participants across all groups. Accounting for an estimated drop out rate of 15%, the total sample size should be increased to 234 participants, with at least 78 participants per group.

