### Statistical analysis

Analyses for this study will be conducted in accordance with both the intention-to-treat (ITT) principle and the per-protocol set (PPS) approach. The ITT analysis will include all randomized participants, and the missing data will be imputed using the Last Observation Carried Forward (LOCF) method, with the most recent observed data carried forward for filling. The PPS will include participants who have completed at least 80% of the prescribed treatment. SPSS 23.0 software will be used for statistical analysis. Quantitative indicators are described using mean, standard deviation, median, 25th percentile and 75th percentile. Categorical indicators are described using frequencies and percentages.

To control the Type I error caused by multiple comparisons, the Bonferroni correction will be adopted for pairwise comparisons of the primary outcome (DHI total score) among the three groups (manual acupuncture vs. sham acupuncture, manual acupuncture vs. western medication, sham acupuncture vs. western medication), with the adjusted significance level set at *p* < 0.017 (0.05/3); for secondary outcomes (DARS scores, dizziness diary indicators including attack frequency, duration and severity), the false discovery rate (FDR) method will be used for multiple comparison correction to balance the Type I and Type II error rates in exploratory analysis of multiple secondary indicators.

Since this study is a multicenter clinical trial, sub-center and corresponding baseline values were incorporated as covariates in the generalized linear model for analysis. Additionally, binary logistic regression was employed to analyze the impact of high versus low expectations on the primary efficacy endpoint across groups. The dependent variable in this analysis was response status, defined as participants showing at least a 50% reduction in total DHI scale score from baseline after 3 weeks of treatment (referred to as responders). The independent variable was the level of expectation (high or low).

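### The three arms cannot isolate the placebo response or show whether betahistine beats placebo, so the Discussion's claim to dissect these components should be narrowed

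*Protocol article*

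**What the plan says.** In its paragraph on the betahistine comparator, the Discussion states as a property of the design that it "permits simultaneous dissection of specific needling effects, non-specific placebo responses, and the actual clinical performance of standard care". The next sentence allows for a particular result: "Even if betahistine shows only mild or placebo-like effects in this study population".

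The arms are set out under Intervention and comparison. All three receive the same secondary stroke prevention, and each adds one thing: manual acupuncture, sham acupuncture or betahistine. For the sham arm, "the SA group will receive sham acupuncture alongside standard secondary prevention treatment". No arm receives background care alone, and none receives a dummy tablet.

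On blinding, Randomization and blinding says that "identical auxiliary devices will be used in both the acupuncture and sham acupuncture groups to maintain blinding for participants", and that "participants in the medication group will not be blinded". The sham arm attends 15 needling sessions over three weeks (Sham acupuncture group). The medication arm takes tablets, and no treatment sessions are described for it (Western medication group).

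The Statistical analysis section lists "sham acupuncture vs. western medication" as one of three Bonferroni-corrected pairwise tests on the DHI total score, each at 0.05/3. The DHI is self-reported (Primary outcome). The contrast appears neither in the objectives that close the Introduction nor in the hierarchy of comparisons in the Discussion.

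**The concern.** To measure a placebo response, a trial needs an arm showing what happens without one. To measure a drug against placebo, it needs a placebo for that drug. This trial has neither: its sham procedure is a control for needling, not for an open-label tablet.

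The Discussion nevertheless presents separation of the placebo response as something the three arms provide, and the plan formally tests the contrast most likely to be read that way. If sham and medication finish close together, a reader of the final report could conclude that betahistine did no better than placebo. If medication finishes ahead, a reader could conclude that the drug works beyond placebo. The data would support neither conclusion. The outcome is a patient-reported score, and the Discussion itself says such scores are prone to expectation and contextual effects.

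**Working it through.** **The plan's own figure.** The Sample size calculation gives the needling means, "assuming a mean DHI score of 21 in the manual acupuncture group, 33 in the sham acupuncture group", with a betahistine mean of 30 and an SD of 20. A one-way ANOVA F-test with means 21/33/30, SD 20 and alpha 0.05 needs 66 per group (power 0.9005). Allowing for dropout, 66/0.85 = 77.6, so 78 per group and 234 in total. The stated figures reproduce and are not in dispute.

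**What each arm contains.** Write the mean DHI improvement in each arm as a sum:

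- B: background course under secondary prevention
- Pn: context effect of blinded needling, taken as equal in manual and sham arms
- A: specific needling effect
- Pt: context effect of an open-label tablet
- D: betahistine effect over a matching placebo tablet

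Then:

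- Manual = B + Pn + A
- Sham = B + Pn
- Medication = B + Pt + D

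Three arm means cannot determine five unknowns. The contrasts give:

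- Manual minus sham = A. This is identified.
- Manual minus medication = (A + Pn) - (D + Pt). This is a comparison of two whole packages, which is legitimate as such.
- Medication minus sham = D + Pt - Pn. This is neither D nor Pn.

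The third contrast is the first minus the second. On the planning means, 12 - 9 = 3, so it brings no information that the other two lack. The sham arm's own change is B + Pn, and without a background-only arm Pn cannot be separated from B.

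**Size of the ambiguity.** Take the planned advantage of medication over sham, 33 - 30 = 3 points. Then D = 3 + Pn - Pt. The documents give no values for Pn or Pt, so the ranges below are assumptions (points of D):

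| Pn | Pt = 0 | Pt = 3 | Pt = 6 |
|---|---|---|---|
| 0 | 3 | 0 | -3 |
| 3 | 6 | 3 | 0 |
| 6 | 9 | 6 | 3 |
| 11 | 14 | 11 | 8 |

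The same observed gap fits a drug effect from -3 to +14, a spread of 17 points against the protocol's minimal clinically important difference of 11. An observed gap of zero would give D = Pn - Pt, which is zero only if the two context effects happen to be equal.

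**Precision, a separate and secondary matter.** With 66 per group, SE = 20 × sqrt(2/66) = 3.48 and the 95% half-width is 6.9 points (6.3 with 78). Power for a 3-point difference is 0.137 at 0.05 and 0.062 at 0.05/3; with 78 per group it is 0.154 and 0.072. Under the plan's own means, about 94% of trials with 66 per group would therefore be non-significant on this test at 0.05/3, and no equivalence margin is stated. More patients would narrow the interval around D + Pt - Pn but would not turn it into an interval for D.

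**The case against.** **The standard-care phrase can be read pragmatically.** The same paragraph frames the betahistine arm as a pragmatic comparison reflecting routine practice. The performance of an open-label drug as used in care is what that arm observes, and manual versus medication compares it fairly with acupuncture as a package. This stands. It would be too strong to say that the design identifies nothing beyond the needling effect.

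**The placebo-like sentence is concessive.** It begins with an if, and its conclusion concerns the added value of acupuncture. A reader might infer that the protocol plans to declare betahistine placebo-like from sham versus medication, but no section says so. This also stands.

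**The direction of bias is not fixed.** A reader might infer bias against the drug, because the Discussion says its choice of sham sites can strengthen the control group's placebo effect. But the tablet's own context effect enters with the opposite sign, and the table contains values of D both above and below the observed 3 points.

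**Low power is not the argument.** The 3-point gap is far below the 11-point threshold. For an 11-point gap with 66 per group, power is about 88% at 0.05 and 77% at 0.05/3. An observed 3-point gap would have a 95% interval of about -3.9 to 9.9, which excludes 11. That interval, however, is for the package difference and not for the drug effect.

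**Cautions are already given.** The Discussion warns about expectancy and about residual sham effects. Its limitations name the unblinded medication arm and leave double-dummy designs to future trials. These cautions are genuine, but they treat the matter as possible bias in outcomes and do not withdraw the statement that placebo responses can be dissected.

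**Conclusion.** The point holds in a limited form. The Discussion asserts a design property the trial lacks: it cannot estimate the size of the placebo response, nor whether betahistine is better than placebo. Sham versus medication, though formally tested on DHI, estimates a difference between two packages that differ in route, contact and blinding. Under the assumed context effects, a 3-point gap is compatible with a drug effect of -3 to +14 points. That range depends wholly on the assumed Pn (0 to 11) and Pt (0 to 6). The lack of identification does not depend on them; it follows from the arms as described.

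The algebra assumes that effects add and that blinding keeps the needling context equal in the manual and sham arms. The primary comparison, the manual versus medication comparison and the sample size are not affected.

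**What to change.** In the Discussion, limit the claim to two contrasts: manual versus sham for the specific needling effect, and manual versus medication for a pragmatic comparison of packages. Add that the trial does not estimate the size of the placebo response or the effect of betahistine over placebo.

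In Statistical analysis, label sham versus medication as an exploratory package comparison reported as a difference with its confidence interval. State that a non-significant result will not be read as betahistine being placebo-like. Keep the 0.05/3 threshold for the other two comparisons. Leaving it unchanged is stricter than two tests would require (0.05/2 = 0.025), but it avoids reopening the error-rate plan.

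No arm, patient or procedure is added. The downside is giving up a claim the design cannot support, and the confirmatory status of one test that serves no stated objective.
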